### Interim analyses {21b}

No interim analyses are planned.

### Methods for additional analyses (e.g. subgroup analyses) {20b}

No additional analyses are planned.

### Methods in analysis to handle protocol non-adherence and any statistical methods to handle missing data {20c}

Primary analyses will be performed based on the intent-to-treat principle. Data completeness will be evaluated and reported at each timepoint in each arm. Linear mixed effect models implicitly account for data missing at random; therefore, multiple imputation of missing observations is not planned.

### Plans to give access to the full protocol, participant level-data, and statistical code {31c}

The trial protocol was prospectively registered in ISRCTN and UMIN-CTR. After the data have been used for all trial purposes, an anonymised version of the dataset will be deposited in an online repository for permanent archiving to use in future studies or meta-analyses.

## Oversight and monitoring

### Composition of the coordinating centre and trial steering committee {5d}

This trial does not have a coordinating centre or trial steering committee. The principal investigator (NY) is responsible for the overall aspects of the trial. The trial team meets every week to oversee the progress of the trial and the completion of tasks and to review necessary changes to the protocol to facilitate the smooth running of the trial. Any major changes to the trial protocol will be reviewed and verified by the Research Ethics Committee.

### Composition of the data monitoring committee, its role, and reporting structure {21a}

Due to the low-risk nature of the intervention, the short duration of the trial, and the fact that interim analyses may not provide necessarily informative results given the nature of the trial, the establishment of a data monitoring committee is not considered necessary. All outcome measures are coded directly into a web programme that cannot be adjusted with all actions being logged. Data will be monitored for completeness and consistency by the trial team. The trial team and statistician will have full access to the final trial dataset.

### Adverse event reporting and harms {22}

All adverse events (AEs) and severe adverse events (SAEs), which may or may not be related to treatment, will be logged throughout the trial. Based on the guidance of Rozental et al. [33], these include the following:Worsening of SAD symptomsNegative events probably emerging from treatment perceived as adverse by the patientEmergence of new psychological symptoms unrelated to those targeted in treatment (e.g. new occurrence of insomnia, panic attacks, etc.).External negative events in participant’s life (e.g. bereavement, other stressors)Other events experienced as negative by the patient during treatment, which may or may not be related to treatment (e.g. issues related to treatment content, increased anxiety during experiments, technical issues).

SAEs are defined as negative events that occur during treatment that require some form of urgent alternative treatment (e.g. substance misuse, deliberate self-harm, suicidal ideation or attempts).

Trial therapists will identify and record their participants’ AE/SAEs when providing iCT-SAD treatment. Participants in both arms will also be asked to report any negative effects experienced during the trial, via a checklist included in the mid-, post-treatment, and 3-month FU assessment packs. AEs will be reviewed on a regular basis by the trial team, including in clinical supervision. SAEs will be brought to the project lead’s attention immediately to consider what actions may be appropriate. This would likely include contact with the participant’s primary psychiatrist*.*

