### Intervention description {11a}

The intervention for this trial is iCT-SAD combined with TAU (iCT-SAD + TAU) (see the above item 6b for more details about TAU). iCT-SAD is an internet-delivered therapist-guided intervention (see ‘Introduction’) [8, 9]. iCT-SAD contains eight core modules which cover key concepts on the nature and maintenance of social anxiety problems, plus 16 optional modules covering common beliefs and difficulties associated with SAD. Participants are supported to complete the core modules across the first two weeks of treatment. Subsequently, the therapist releases those optional modules that are particularly relevant to each participant’s concerns. Participants are also supported to conduct ‘behavioural experiments’, in which they test out their feared concerns in social situations whilst focussing their attention externally and dropping their safety behaviours. Trained therapists support participants by telephone, text messages, and video calls via webcam. Each telephone call lasts approximately 20 min and is used to review questionnaire measures, progress with modules and behavioural experiments, and planning for the coming week. To support initial engagement, two phone calls per week are scheduled during the first 2 weeks of treatment, followed by once-weekly phone calls until the end of the 14-week treatment phase. During the subsequent follow-up period, up to three booster calls are scheduled at monthly intervals.

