### Outcomes {12}

The principal assessment points for outcome measures will be baseline (week 0), mid-treatment (week 8), post-treatment (week 15), and 3-month follow-up (week 27, intervention arm only). The primary assessment timepoint is post-treatment (week 15).

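### Adverse events have an extra recording route in the iCT-SAD arm, and no stated route takes a TAU serious event to the trial between the week 8 and week 15 checklists

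*Protocol article*

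**What the plan says.** The section Adverse event reporting and harms {22} undertakes to log every AE and SAE for the whole of the trial, whether or not related to treatment, and to bring SAEs to the project lead at once. It names two sources. Therapists record what they find in the people they treat, and self-report covers everyone: "AE/SAEs when providing iCT-SAD treatment. Participants in both arms will also be asked to report any negative effects experienced during the trial". According to the same section, this self-report is gathered "via a checklist included in the mid-, post-treatment, and 3-month FU assessment packs".

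Other sections determine what this means in each arm:

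- Intervention description {11a}: "two phone calls per week are scheduled during the first 2 weeks of treatment, followed by once-weekly phone calls until the end"; the course lasts 14 weeks. In the follow-up period, "up to three booster calls are scheduled at monthly intervals".
- Outcomes {12} lists the last assessment as "3-month follow-up (week 27, intervention arm only". The abstract agrees, and in Table 1 the TAU arrow ends at week 15.
- Eligibility criteria {10} and Explanation for the choice of comparators {6b}: participants must be able to see their psychiatrist in person at least monthly, and safety and clinical risk are assessed at those visits.
- Section {22} also states: "SAEs are defined as negative events that occur during treatment".

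No section says that the psychiatrist reports events to the trial. Where sections {11b} and {22} describe contact, it runs from the project lead to the psychiatrist once an event is already known.

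**The concern.** One arm has a clinician of the trial in regular contact who is charged with recording events. The other has two questionnaires. Events counted from both sources are not ascertained alike, so a table of total AEs by arm would mix a treatment difference with a difference in how hard the trial looked. A later analysis plan can choose which source to tabulate, but it cannot recover events that were never collected.

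The second issue is reporting. The promise of continuous logging and immediate escalation needs a channel by which the trial learns of an event. For TAU between checklists, none is stated. This carries some weight because the protocol has no data monitoring committee, no steering committee and no audit, so the event log is the main instrument of trial-level safety oversight.

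**Working it through.** The protocol gives no figure on event capture, so there is none to reproduce. The check is a count of stated recording opportunities, followed by an illustration under declared assumptions.

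**1. Stated recording opportunities**

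Scheduled calls to week 14: 2 per week × 2 weeks + 1 per week × 12 weeks = 4 + 12 = 16.

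| Period | iCT-SAD + TAU | TAU alone |
|---|---|---|
| To week 15 | 16 calls + 2 checklists = 18 | 2 checklists |
| After week 15 | up to 3 booster calls + 1 checklist | none stated |

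The calls are opportunities to record. The text does not say that each one includes an adverse-event enquiry.

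**2. Delay before a TAU event can enter the log by the stated route**

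The checklists fall at weeks 8 and 15. The longest waits are 8 − 0 = 8 weeks and 15 − 8 = 7 weeks. For an event equally likely at any time over the 15 weeks, the mean wait is (8 × 4 + 7 × 3.5) / 15 = 56.5 / 15 ≈ 3.8 weeks. In the iCT-SAD arm the next scheduled call is at most about one week away while weekly calls run.

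**3. Direction and possible size of the distortion**

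Let s be the probability that the checklist captures an event and t the probability that the therapist does, taken as independent, with equal true rates in the two arms. Neither s nor t is in the document; both are assumptions. The apparent ratio, iCT-SAD to TAU, is [1 − (1 − s)(1 − t)] / s.

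| s | t = 0.3 | t = 0.6 |
|---|---|---|
| 0.5 | 0.65 / 0.50 = 1.30 | 0.80 / 0.50 = 1.60 |
| 0.7 | 0.79 / 0.70 = 1.13 | 0.88 / 0.70 = 1.26 |
| 0.9 | 0.93 / 0.90 = 1.03 | 0.96 / 0.90 = 1.07 |

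The ratio exceeds 1 whenever therapists pick up anything that the checklist misses. Its size depends wholly on s and t.

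**4. Texts set side by side**

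- Section {22} speaks of both arms and of a checklist in the 3-month pack. Outcomes {12}, the abstract and Table 1 give TAU no 3-month assessment.
- Section {22} logs events over the whole trial but defines SAEs by their occurrence during treatment. How this applies to iCT-SAD follow-up between weeks 15 and 27, and to the TAU arm, is left to interpretation.

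**The case against.** The strongest reply is that no harms comparison is planned. Harms are not among the objectives, and under section {20a} any result without a named test is only described. The same checklist is given to both arms at weeks 8 and 15, which is what a fair comparison needs. This stands to the extent that no specified test is invalidated. A descriptive table of total events by arm would still carry the imbalance, and nothing in the text restricts it to the common source.

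A reader might infer that TAU serious events go clinically unnoticed for weeks. The document does not support that: both arms are to be seen in person at least monthly for safety monitoring. The gap lies in reporting to the trial. A reader might also infer that therapists ask about adverse events at every contact. The text says only that they record them while delivering treatment, and {11a} describes the calls as reviewing questionnaires, modules and experiments and planning the week.

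Section {11d} could be offered as a second route, since it has treatment changes and their reasons recorded throughout, and an SAE by definition calls for urgent alternative treatment. But it names neither reporter nor timing, and it covers treatment changes rather than events. A full protocol might hold further notification detail. The article nevertheless states its sources, and they are unequal and at odds with its own follow-up schedule.

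Finally, the distortion would not make iCT-SAD look falsely safe. That is correct, and it limits the consequence. The longer follow-up of the intervention arm is also an openly stated design feature: TAU participants are offered iCT-SAD after week 15, so no comparable TAU period exists.

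**Conclusion.** The point holds in a limited form. Ascertainment differs by arm as written, and pooled AE totals by arm would tend to be higher under iCT-SAD at equal true rates. That direction rests on one assumption, that therapists detect some events the checklist does not. The size cannot be computed from the document; the 1.03 to 1.60 range illustrates assumed capture rates and is not an estimate. It would be too strong to call the trial's harms conclusion uninterpretable, because a like-for-like comparison is available from the common checklists.

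By the stated routes, a TAU SAE can stay out of the trial log for up to 8 weeks before week 8 and up to 7 weeks thereafter. That sits badly with continuous logging and immediate escalation. The wording on both arms and the 3-month checklist is a plain inconsistency. None of this bears on the primary efficacy analysis.

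**What to change.** - State that any by-arm AE summary uses only the common participant checklists at weeks 8 and 15. Some difference will remain, because participants are unblinded and section {18a} has the two arms complete questionnaires on different platforms.
- Report therapist-recorded events and week-27 events separately for iCT-SAD, without comparison with TAU.
- State how an SAE known to the primary psychiatrist from the existing monthly visits reaches the trial log, in the same way for both arms.
- Reconcile the both-arms, 3-month wording in {22} with Outcomes {12} and Table 1, and reconcile the SAE definition with the commitment to log events throughout the trial.

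The cost is a short notification instruction for psychiatrists who are already to see every participant, a split AE table, and a few wording changes. No visit or assessment is added.

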### Frequency and plans for auditing trial conduct {23}

No audit is planned for trial conduct. The principal investigator is obliged to and will inform the Research Ethics Committee in case of any major deviations from the trial design approved by the Committee.

### Plans for communicating important protocol amendments to relevant parties (e.g. trial participants, ethical committees) {25}

All protocol amendments will follow the Research Ethics Committee revision process and will be approved prior to their implementation. Where necessary, the trial team members will be informed via email or in clinical supervision. Deviations from the published protocol will be documented in the trial registration on ISRCTN and UMIN-CTR.

#### Dissemination plans {31a}

The findings of this trial will be disseminated to academic and professional audiences via publications in peer-reviewed journals and presentations at academic conferences, and to the broader public via public talks and media/press releases. All findings from the trial, whether negative or positive, will be reported.

## Discussion

Investigating the efficacy of internet interventions in different cultural contexts is an important step in determining whether the potential global reach of such treatments can be achieved. This trial provides a valuable examination of iCT-SAD combined with usual care, which is a good reflection of how the treatment might subsequently be provided in routine settings. It offers a further contribution to the small but growing literature on the international dissemination of internet interventions and to our understanding of treating social anxiety in Japan. A limitation of this trial is that an active comparator arm will not be employed, meaning the specific effects of iCT-SAD relative to other internet interventions cannot be revealed.

## Trial status

Protocol version 1.0, 2023-October-18. The study is planned to begin in November 2023 and is estimated to be completed in December 2025. Recruitment is planned to begin in January 2024 and is estimated to be completed in May 2025.

## Data Availability

A de-identified individual-level dataset will be made available through a publicly accessible online repository after the primary findings of this trial are published.

## Abbreviations

ADIS-5: Anxiety and Related Disorders Interview Schedule for DSM-5
AE: Adverse events
CT: Cognitive therapy
CONSORT: Consolidated Standards of Reporting Trials
DSM-5: Diagnostic and Statistical Manual of Mental Disorders, Fifth Edition
FU: Follow-up
GAD-7: Generalised Anxiety Disorder Questionnaire 7-item
iCT-SAD: Internet-delivered cognitive therapy for social anxiety disorder
INDICE: Internet Data and Information Center for Medical Research
ISRCTN: International Standard Randomized Controlled Trials
LSAS: Liebowitz Social Anxiety Scale
NICE: National Institute for Health and Care Excellence
PHQ-9: Patient Health Questionnaire 9-item
SAD: Social anxiety disorder
SAE: Severe adverse event
SAQ: Social Attitudes Questionnaire
SBQ: Social Behaviour Questionnaire
SCID-5: Structured Clinical Interview for DSM-5 Disorders
SCQ: Social Cognitions Questionnaire
SPWSS: Social Phobia Weekly Summary Scale
TAU: Treatment as usual
UMIN: University Hospital Medical Information Network
UMIN-CTR: UMIN Clinical Trials Registry
WSAS: Work and Social Adjustment Scale
